ISCM also explains how historical trauma, systematic oppression, and cultural displacement impact Indigenous health, while emphasizing cultural resilience and traditional practices as protective factors. It aligns with SCT by highlighting the dynamic interaction between personal, behavioral, and environmental influences, particularly through self-efficacy and observational learning within community settings. Because ʻIKE Kūpuna utilizes hula as a preventative measure for vascular dementia in NHPI populations, both SCT and ISCM help to explain its effectiveness. ISCM underscores how cultural identity and intergenerational knowledge transmission strengthen well-being, while SCT highlights how participation, role modeling, and social support encourage engagement and health behavior change.

Fig. 2 depicts our conceptual model with the hypothesized relationships between study variables (Fig. 2). We expect that *‘IKE Kupuna* will lead to improvements in vascular ADRD risk factors and cognitive functioning through a causal path that is mediated by improvements in dance and other forms of physical activity; in diet, sleep, stress, and other psychosocial factors; and in cultural connection and social engagement.

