Consistent with our CBPR approach, our community partners wanted to reduce the physical and mental burden on the older NHPI adults by lessening the overall assessment duration (i.e., no longer than 1 h) and the number of assessment measures. Thus, we limited the assessments to only capturing our primary (i.e., vascular risk factors for ADRD and subjective cognitive complaints) and secondary outcomes (i.e., other measures of cognitive performance, physical function, and mental health) to answer our primary research aim, which was to determine the intervention effect on improving vascular and cognitive risk factors of ADRD. We also include measures to capture potential mediators depicted in Fig. 2, such as depression, substance use, sleep behaviors, diet, and physical activity.

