Linear or logistic hierarchical models will be specified to model continuous or binary versions of the outcomes (Table 3), respectively. Normality assumptions will be assessed by Q-Q plots and transformations when appropriate. All models will include a cohort-level random intercept. Analyses will first estimate the effect of the intervention on each of the primary outcomes separately for 3, 8, and 12 months. If doing so improves model fit, we will also fit a model that includes all time points and a cohort-level random slope over time. Time (baseline and 3, 8, and 12-months) will be modeled as a categorical and continuous variable. If the model fit is not significantly different, we will retain the latter as the more parsimonious specification. All models will include a binary indicator for randomization to the immediate intervention arm. We will include a coefficient for the intervention × time interaction to estimate divergence between the 2 study arms during follow-up. This term represents the statistical test of the intervention for improving the outcome. For sensitivity analysis, we will adjust for individual-level covariates for which there is evidence of imbalance between the two study arms at baseline. Lastly, we will conduct exploratory analyses to evaluate potential mediation of the intervention effect by relevant covariates (e.g., better sleep quality as an explanation for improved cognitive function) by including the potential mediators in the model to estimate controlled direct effects of the intervention. Results for inferential analyses will be reported as mean or risk differences and ratios with 95 % confidence intervals.

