**Lifestyle and Physical Function**					
Physical activity scale		X		X	X
Dietary		X		X	X
Social Habit		X		X	X
Sleep		X		X	X
IADL		X		X	X

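### The exploratory mediation analysis adds post-randomisation mediators to the outcome model without addressing shared causes of mediator and outcome, so it can show mediation where none exists

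*Protocol article*

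**What the plan says.** The Statistical analysis and power section (2.3.5) closes its modelling plan with mediation: "Lastly, we will conduct exploratory analyses to evaluate potential mediation of the intervention effect by relevant covariates". The example given is "better sleep quality as an explanation for improved cognitive function", and the method is to proceed "by including the potential mediators in the model to estimate controlled direct effects of the intervention".

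The Measures section (2.3.4) names the candidates: "We also include measures to capture potential mediators depicted in Fig. 2, such as depression, substance use, sleep behaviors, diet, and physical activity". Conceptual grounding (2.1.2) gives the hypothesis behind them, that benefit arises "through a causal path that is mediated by improvements in dance and other forms of physical activity" and through diet, sleep, stress, other psychosocial factors, cultural connection and social engagement.

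Two other statements bear on the point. The outcome models start visit by visit: "Analyses will first estimate the effect of the intervention on each of the primary outcomes separately for 3, 8, and 12 months". Covariate adjustment is described once, as a sensitivity analysis: "we will adjust for individual-level covariates for which there is evidence of imbalance between the two study arms at baseline".

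Table 2 schedules the mediators (for example the row "Physical activity scale", and the rows for diet, social habit, sleep and depressive symptoms) at baseline, 8 and 12 months. The four cognitive measures are taken at screening or baseline, then at 8 and 12 months. Neither set is taken at 3 months. The text does not say which visit's mediator value enters the model.

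**The concern.** Randomisation protects the comparison of arms. It does not protect the relation between a mediator and an outcome that both arise after randomisation. Once the mediator is in the model, the arm coefficient is a direct effect only if no uncontrolled common cause of mediator and outcome remains and the outcome does not drive the mediator.

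The adjustment described uses the wrong criterion for this purpose. A common cause that is perfectly balanced between arms still biases the mediator-adjusted arm coefficient. Such causes are plausible here. CCI is a subjective measure and QDRS is self-rated, while sleep, diet and activity come from questionnaires, so mood or reporting style can move both sides. The Informed consent and screening section itself notes that depression can distort screening for cognitive impairment.

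At stake is the explanatory claim. This is the only analysis the article describes that examines the hypothesised path, and as described it can support that path when it is absent.

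**Working it through.** **Scale.** The article gives no figure for the mediation analysis. Its detectable standardised effect for cognitive outcomes, 0.38 to 0.56, is used below as one scale. With 8 groups per arm, m = 9 × 0.8 = 7.2, intra-cohort correlation 0.01, and two-sided alpha 0.05 (sidedness is assumed):

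MDE = (1.960 + 0.842) × √{2[2(1−ρ)(0.99) + 2(7.2)(0.01)] / (8 × 7.2)}

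- ρ = 0.8: 2.802 × √(1.08/57.6) = 0.384
- ρ = 0.5: 2.802 × √(2.268/57.6) = 0.556

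Both agree with the article.

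**Shared causes, no true mediation.** Let the arm shift the mediator by a and the outcome by τ (SD units). Let r be the residual mediator-outcome correlation due to common causes, and let the mediator have no effect on the outcome. Adding the mediator turns the arm coefficient from τ into τ − a·r, so the apparent share mediated is a·r/τ. None of a, τ and r is in the documents for this purpose; all are assumptions.

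| a | τ | r | Apparent share (truth 0%) |
|---|---|---|---|
| 0.5 | 0.4 | 0.2 | 0.10/0.4 = 25% |
| 0.5 | 0.4 | 0.3 | 0.15/0.4 = 37.5% |
| 0.5 | 0.4 | 0.4 | 0.20/0.4 = 50% |
| 0.38 | 0.38 | 0.1, 0.3, 0.5 | 10%, 30%, 50% |
| any | any | 0 | 0% |

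A simulation of 2,000 trials per setting (115 analysed, 8 cohorts per arm, intra-cohort correlation about 0.01) agrees:

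- With a = τ = 0.38, the arm coefficient falls from 0.38 to 0.34, 0.27 and 0.19 at r = 0.1, 0.3 and 0.5.
- At r = 0.3 the non-causal mediator is significant in about 91% of trials. Adding the common cause to the model restores about 0.38.
- Over a = 0.20 to 0.56, τ = 0.38 or 0.56 and r = 0.1 to 0.5, the apparent share runs from 4% to 73%.
- With τ = 0, a = 0.38 and r = 0.3, a false direct effect of −0.11 appears (−0.38 × 0.3), rejected in 10% of trials against a nominal 5%.

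**Reverse causation at the same visit.** If the outcome drives the mediator with standardised path p and the arm reaches the mediator only through the outcome, the arm effect on the mediator is p·τ and the outcome-on-mediator slope is about p. The apparent share is then about p²: 9% at p = 0.3 and 25% at p = 0.5. The simulation gives the same.

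**Timing.** For month-8 cognitive outcomes, the month-8 mediator is the only post-baseline value that exists, so same-visit use is forced. For month 12, which the article calls its primary endpoint, either the month-8 or the month-12 mediator could be used. At month 3 these mediators are not measured.

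**Effect of the remedy.** Take a = 0.5, τ = 0.4, a stable shared cause and within-person correlation 0.5 (the lower of the article's two values, here assumed for mediator and outcome alike). At r = 0.3:

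- Regressing the month-8 mediator on baseline mediator and outcome gives slopes (0.5 − 0.09)/0.91 = 0.451 and (0.3 − 0.15)/0.91 = 0.165.
- Its residual variance is 1 − 0.451(0.5) − 0.165(0.3) = 0.725.
- Its residual covariance with the month-12 outcome is 0.3 − 0.451(0.3) − 0.165(0.5) = 0.082.
- The slope is 0.082/0.725 = 0.114, and the apparent share is 0.5 × 0.114/0.4 = 14%.

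The same steps give about 9% at r = 0.2 and 21% at r = 0.4. Simulations with stable or partly visit-specific shared causes fall in the range 8% to 22%.

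**The case against.** **Same-visit adjustment is not stated.** A reader might infer that the plan fixes it throughout. It does not: Table 2 forces it only for month-8 cognitive outcomes and leaves month 12 open. This objection stands.

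**A controlled direct effect is a legitimate estimand.** A reader might infer that it is simply the wrong target. The article asks only to evaluate potential mediation and promises no mediated share, so that reading goes too far. The percentages above are a way to express the bias, not a quantity the plan proposes to report. Total minus controlled direct effect does equal an indirect effect only without arm-by-mediator interaction, which matters if the results are read as a share.

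**This is detail for the SAP.** Mediator timing, the confounder list and sensitivity analyses can be left to a fuller document, and the imbalance adjustment belongs to the main models. That stands for the omissions. It does not cover the method the article does state, which is to add mediators to the outcome model and read a direct effect. The only adjustment rule given alongside does not serve that purpose.

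**It is exploratory and in neither Specific Aim.** Correct, and this limits the consequence. The label lowers the strength of claim but does not remove bias.

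**The remedy keeps part of the fault.** Also correct. With a purely stable shared cause, same-visit adjustment that includes baseline mediator and outcome leaves the same share as the month-8 version, so there the gain comes from the baseline terms. Lagging helps when some shared causes are specific to a visit. It does not fully exclude reverse causation, because a month-8 outcome that drove the month-8 mediator persists to month 12.

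**Conclusion.** The point holds as a minor one. The stated method conditions on post-randomisation variables, and the adjustment described does not address shared causes of mediator and outcome, so it can show mediation where there is none. At assumed effects of 0.5 SD on the mediator and 0.4 SD on the outcome and residual correlations of 0.2 to 0.4, the false share is about 25% to 50%. It is zero if there are no shared causes and no reverse causation, and the documents give no figure that fixes where the trial lies. The primary intervention effect does not depend on this analysis, and nothing here suggests that the trial's main comparison is biased.

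**What to change.** For the 12-month outcome, state that the month-8 mediator is used, with adjustment for baseline mediator, baseline outcome, age, sex and education. Add a sensitivity analysis for unmeasured mediator-outcome confounding. Report the result as hypothesis-generating, not as evidence that the effect runs through the mediator, and describe month-8 same-visit coefficients as associations only.

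All these variables are already collected, so the cost is a little analysis work. The downside is that participants without a month-8 visit must be imputed or drop out of this analysis. The change reduces the bias without removing it, and the report should say so.

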## Results

3.

‘Ike Kupuna is a 5-year project that started in September 2021 and is expected to be completed by November 2025. The enrollment of participants began on September 2, 2022, and is planned to end on November 30, 2024. The protocols for this project have been approved by the Institutional Review Board of the University of Hawai’i (2022–00090) and are registered in ClinicalTrials.gov (NCT05534607). To date, activities to achieve Specific Aim 1 have been completed and the protocols for Specific Aim 2 presented here reflect the modifications made based on the results of Specific Aim 1. As hypothesized, the adapted hula-based intervention incorporates culturally tailored education to promote a healthy diet, culturally-based exercises to improve cognitive function, and community and social support. For Specific Aim 2, we expect the hula-based intervention to be superior to the waitlist control condition in improving vascular risk factors, subjective cognitive complaints, and objective cognitive function.

## Discussion

4.

Given the high risk of ADRD among NHPI, our ʻIKE Kūpuna project seeks to reduce this risk by designing and testing a novel, culturally grounded lifestyle intervention among NHPI with the vascular risk factors for ADHD and very early signs of cognitive problems. Our project features several important innovations. First, we test an authentic cultural practice as a paradigm-shifting health promotion and disease prevention strategy aimed at preventing cognitive decline in NHPI, a high-risk population that has been largely excluded from ADRD research. Secondly, our hula program seeks to promote healthy lifestyles consistent with NHPI values and aspirations and thus likely to lead to sustainable behavior change for at-risk NHPI individuals. Finally, the use of a culturally grounded intervention that leverages a prevalent and assessable cultural practice, such as hula, can be naturally sustainable in NHPI communities with existing resources.

A strength of this project is our use of hula, a traditional cultural practice, for ADRD prevention in NHPI. This approach has a strong theoretical foundation supported by preliminary data. Its popularity and accessibility will ensure that this adapted hula-based intervention is appealing and sustainable. The primary requirement of our programs is the presence of a trained kumu, and there are hundreds of kumu present on a global level (Mele.com, 2010). Another strength is the inclusion of both subjective and objective cognitive measurements. Considering the mild complaints many participants will report, relying solely on cognitive performance could miss important improvements in both symptoms and longer-term outcomes among individuals with SCI.

There are also some notable limitations. A potential challenge is our wait-list control design, which limits the feasible length of follow-up in the GRT. Our partner communities believe it is unethical to withhold the intervention from any participant, given its previous effectiveness for lowering blood pressure beyond 12 months. Notwithstanding, our 12-month design will permit us to assess within-person cognitive change over time, and we are mainly conducting a primary prevention study to reduce risk years before dementia onset by improving vascular risk factors for ADRD. Another potential challenge will be ensuring the consistency of the intervention across the five CBO. Thus, we will provide robust training and conduct regular fidelity checks. Additionally, we anticipate that our participant sample will include more women than men, given our previous experience with intervention research. Thus, we will strive to achieve a balanced representation of the sexes. Also, the absence of validated cognitive assessment tools in NHPI communities can result in potential measurement bias or be hindered by linguistic or cultural factors. We are currently performing factor analyses on the tools used in this study to determine its construct validity. Finally, because this research is being done in Hawai’i, where 25 % of the population are NHPI, our approach and results may not be as easily replicated or generalizable to NHPI in the continental U.S. However, as we noted earlier, there are numerous hula schools throughout the U.S.

## Figures and Tables

**Fig. 1. F1:**
[figure not shown]
Group-randomized Hula trial.

**Fig. 2. F2:**
[figure not shown]
Conceptual model.

**Table 1 T1:** Summary of SCI and MCI eligibility based on the three cognitive measures.

CCI	NSCT	QDRS	Eligibility
<6	≥36	<2	Not Eligible (Normal)
Any	Any	≥6	Not Eligible (mild-severe ADRD)
≥6	Any	<2	Eligible (SCI)
Any	Any	2–5.5	Eligible (MCI)

**Table 2 T2:** Summary of data collection visits.

Measure/Variables	Time Point				
	Screening	Baseline	3 mo	8 mo	12 mo
**Cognitive Function**					
Cognitive Change Index	X			X	X
Quick Dementia Rating Scale	X			X	X
Number Symbol Coding Test	X			X	X
Cognivue		X		X	X
**Vascular Risk Factors**					
Blood cholesterol		X	X	X	X
Hemoglobin A1c		X	X	X	X
Blood pressure		X	X	X	X
Body-Mass-Index		X	X	X	X
**Lifestyle and Physical Function**					
Physical activity scale		X		X	X
Dietary		X		X	X
Social Habit		X		X	X
Sleep		X		X	X
IADL		X		X	X
**Psychosocial, Cultural, and Mental Health**					
Cognitive and leisure activities		X		X	X
Depressive symptoms		X		X	X
Depression screening	X				
**Other Variables**					
Demographics		X			
Neighborhood factors		X			X
Family History		X			X
Bilingualism		X			
Occupational Scale		X			X

**Table 3 T3:** Power for group-randomized trial vascular outcomes.

Outcome	Minimum detectable difference between treatment arms		SD
	*ρ* _ *m = 0.8* _	*ρ* _ *m = 0.5* _	
Blood lipids	13.4	19.7	35
Hemoglobin A1c	0.8	1.2	2.2
Systolic blood pressure	5.8	8.4	15
Diastolic blood pressure	4.2	6.2	11
Body mass index	3.1	4.5	8

SD = standard deviation; ρ_m_ = *within-person correlation over time*.

## Abbreviations:

ADRD: Alzheimer’s disease and other related dementias
CBO: community-based organizations
GRT: group-randomized trial
NHPI: Native Hawaiians and Pacific Islanders
SCI: subjective cognitive impairment
MCI: mild cognitive impairment
